## Abstract

**Background:**

Asthma is the leading source of unscheduled hospitalisation in Australian children, with a high burden placed upon children, their parents/families, and the healthcare system. In Australia, there are widening disparities in paediatric asthma care including inequitable access to comprehensive ongoing and planned asthma care for children.

**Methods:**

The Asthma Care from Home Project is a comprehensive virtually enabled asthma model of care that aims to a. supports families, communities and healthcare providers, b. flexible and locally acceptable, and c. allow for adoption of innovations such as digital technologies so that asthma care can be provided “from home”, reduce potentially preventable asthma hospitalisation, and ensure satisfaction at a patient, family, and healthcare provider level. The model of care includes standardisation of discharge care through provision of an asthma discharge resource pack containing individual asthma action plan, follow-up letters for the child’s general practitioner (GP) and school/child care, and access to online asthma educational sessions and resource; post-discharge care coordination through text message reminders for families for regular GP review, email correspondence with their child’s GP and school/childcare; and virtual home visits to discuss home environmental triggers, provide personalised asthma education and respond to parental concerns relating to their child’s asthma. This study is comprised of three components: 1) a quasi-experimental pre/post impact evaluation assessing the impact of the model on healthcare utilisation and asthma control measures; 2) a mixed-methods implementation evaluation to understand how and why our intervention was effective or ineffective in producing systems change; 3) an economic evaluation to assess the cost-effectiveness of the proposed model of care from a family and health services perspective.

**Discussion:**

This study aims to improve access to asthma care for children in rural and remote areas. Implementation evaluation and economic evaluation will provide insights into the sustainability and scalability of the asthma model of care.

## Background

Asthma is a complex disease and remains one of the most common disorders worldwide [1]. Our improved understanding of asthma has led to advances in management and asthma outcomes have improved, particularly in high income countries like Australia. However, health disparities endure as children continue to have a high associated burden of care, high levels of uncontrolled asthma, and increased healthcare utilisations [2]. Within Australia, 1 in 10 children have a diagnosis of asthma, and it leads to more than 20,000 unscheduled hospital presentations in children with asthma, costing the health system more than $300 million annually [3]. This high rate of hospitalisation is not only associated with high costs to the healthcare system but also results in school absenteeism, significant burden on families from days missed from work and psychological stress [4].

Children living in rural and remote settings are particularly disadvantaged and face multiple barriers to asthma care. The highest burden of care and mortality rates from asthma in Australia are reported in rural and remote communities despite having lower prevalence rates compared to their urban counterparts [5]. In the state of New South Wales (NSW), there are around 50,000 children with asthma living in rural and remote regions [6, 7]. Studies from the US suggest rural children are significantly more likely to have moderate to severe asthma compared to urban children (46% vs 35%) [8]. Similar studies are yet to be done in Australia on a large scale. In addition, rural families have on average 20% less disposable income than families from urban areas, they have less access to primary care, journeys to seek healthcare are eight times longer, and more time is spent absent from work or school due to healthcare appointments compared to urban-based families [7, 9].

At the core of asthma management is the focus on establishing effective asthma control and risk reduction of morbidity and mortality. Traditionally, asthma management in children has required regular attendance to healthcare professionals (General Practitioners (GPs) Paediatricians and/or Respiratory specialists) for review of asthma control, monitor lung function parameters, asthma education, assess medication adherence and response, and titration of pharmaceutical therapy as necessary [10]. The recent COVID-19 pandemic has however enforced changes in clinical practice both in Australia and internationally at short notice, with less face-to-face interactions, increased use of emergency departments (EDs) for primary care, and a new reliance on technology to ensure continued access to care. With the emergence of e-health and digitally based interventions, the COVID-19 pandemic has highlighted and quickened the use of these interventions in daily practice, however its specific role in paediatric asthma care needs more thorough evaluation [10].

The current model of care for childhood asthma in Australia, which is hospital-centred, is fragmented, complex and inadequate [11]. Our prior work has demonstrated several gaps in childhood asthma care in Australia. Firstly, Australian children receive guideline adherent asthma care on around 60% of occasions [12]. Within NSW, post-discharge asthma management pathways vary between local health districts (LHDs), between hospitals in the same LHD and within departments of the same hospital. On average four to six different asthma clinical practice guidelines and asthma action plans were used in each LHD [13]. Additionally, asthma education provided in hospitals was often non-formal and rarely involved key topics such as knowledge of asthma, asthma control and regular medical review. Lastly, there is currently no system to ensure subsequent follow-up with General Practitioners (GPs) after discharge from hospitals and linkages with community-based services are almost non-existent [13], highlighting the need for a comprehensive integrated model of paediatric asthma care.

Systematic review and meta-analysis from our team have shown that a multicomponent comprehensive asthma model of care that includes i) asthma self-management education, ii) active care coordination connecting patients/families with acute, primary and community-based services, and iii) in-home environmental assessment can reduce asthma hospital presentations by 80% [11]. Subsequently we evaluated a co-developed integrated model of asthma care, co-designed with parents and professionals, at Sydney Children’s Hospital (SCH), which included the provision of a standardised asthma discharge pack for children and parents containing an individualized Asthma Action Plan, information pack and discharge instructions (including recommended follow-up with a GP), streamlined appointments with a GP post-discharge from the hospital, and text message reminders to parents reminding them to follow-up with GP and encouraging attendance to an asthma education session. This model of care led to a 56% reduction in number of children who presented frequently to the ED with asthma [14]. Although the model of care was effective in a large metropolitan children’s hospital, its value in rural areas cannot be assumed and translation of the successful model into rural areas requires robust evaluation.

Therefore, leveraging digital technology and building on our existing work on paediatric asthma, we will implement and evaluate a comprehensive and flexible model of care that ensures standardisation of asthma discharge from hospital, active care coordination between acute and primary care services, establishes linkage with a child’s school/childcare services and delivers home-based follow up services to provide optimal health outcomes in children with asthma living in rural NSW.

## Hypotheses and aims

We hypothesise that a comprehensive virtually enabled asthma model of care that leverages digital technologies can provide continuity of care, improve asthma quality of life and lead to reduction in unscheduled hospital presentations in children with asthma aged 5–12 years living in rural NSW. We further hypothesise that our proposed model of care will reduce the cost of care devoted to this patient cohort and help to alleviate financial pressures facing families as a result of a child’s asthma diagnosis.

Asthma Care from Home aims to evaluate the impact (aim 1), implementation (aim 2) and cost effectiveness (aim 3) of a comprehensive virtually enabled asthma care initiative in three rurally based LHDs in NSW that a. supports families, communities and healthcare providers, b. is flexible and locally acceptable, and c. adopts innovations such as digital technologies so that asthma care can be provided ‘from home’ when necessary, thereby not only reducing the significant burden of potentially preventable asthma hospital presentations but also ensuring patients’, parents/carers and families satisfaction with healthcare delivery.

This project comprises of three related research questions:

What is the impact on asthma-related health system utilisation, child’s health related quality of life and parent/carer’s experiences?What is the cost effectiveness and cost impact for both the child’s family and the healthcare system by adopting this model?Can these results be used to support State-wide scale-up?

## Study methods

### Study design and setting

Our study will be an integrated impact, implementation and economic evaluation embedded within a quasi-experimental pre and post interventional trial at three large rural Local Health Districts (LHDs) in NSW, Australia: Northern NSW Local Health District (NNSWLHD), Southern NSW Local Health District (SNSWLHD) and Western NSW Local Health District (WNSWLHD). Ethical approval was granted by the Sydney Children’s Hospital Network Human Research Ethics Committee in November 2022 (2022/ETH01946). Site specific Research Governance was granted across all participating Local Health District Research Governance by March 2023 (2022/STE03422, 2022/STE03423, 2022/STE03424 and 2022/STE03425).

### Study population

Between March 2023 and June 2024, children aged between 5–12 years old presenting to ED on one or more occasions or admitted to the general paediatric ward on one or more occasion in the last 12 months with asthma at selected study hospital sites within the three LHDs will be eligible to participate in the study. For those that fulfil all eligibility criteria (Box 1), each participant will be followed for a period of 12 months after enrolment. Informed written consent was sought from parents/carers of eligible children electronically via REDcap software.

Box 1Inclusion criteriaChildren aged between 5–12 years old.1 or more ED presentations or 1 or more hospital admission in the last 12 monthsChildren with current or history of physician-diagnosed asthmaChildren attended EDs or admitted to general paediatric wards with asthma exacerbation or asthma-related illnesses (e.g. wheeze) at hospitals within the three participating LHDs during the study periodParents/carers of non-English speaking background but understand English and do not require interpreter.Exclusion criteriaChildren with complex conditions e.g., genetic disorders, complex cardiac diseases etc.Children with high-risk and complex asthma who are already known to tertiary paediatric respiratory specialists.Children with significant developmental delays or comorbidities that will significantly limit their ability to participate in the study.Both parents/carers who do not understand English and require interpreterFamilies who do not have permanent housing e.g., live in a shelter.

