### Aim 1: Impact assessment

#### Data collection

Changes in health service use for participating children will be evaluated by comparing the period of up to 5 years prior to their enrolment into the program (pre-intervention) and the period of up to 12 months following enrolment (post-intervention). This information will be gathered primarily from electronic care records at baseline (retrospectively gathering data on health service use in previous 5 years) and 12 months post-enrolment. Five years data pre-enrolment will be used to account for disruption from the COVID-19 pandemic.

As we are following up participants through time in each site, the pre- intervention time period of health service use for each participating site will serve as its own control for the post-intervention time period of health service use, that is, temporal control.

*Outcomes measures*. All outcome measures for the impact assessment will be assessed at baseline, 6 months, and 12 months post-intervention (Table 1). We will measure the changes over time (i.e., pre-intervention at baseline and post-intervention at 6-month and 12-month), and differences between intervention and temporal control groups on all indicators.

**Table 1 pone.0304711.t001:** Outcome measures of the impact assessment.

Outcome	Measure(s)	Source	Time point

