#### Data analysis

Interrupted time series (ITS) analysis will be used to assess the change in the time series patterns (intercept and slope) of health service use before and after intervention.

ACT score, asthma related quality of life, medication adherence, parent and child quality of life and family reported experiences will be compared at enrolment, 6 and 12 months after enrolment into the service. We will describe the outcomes at each time point using mean, standard deviation, median, and inter-quartile range. Since each participant will have three repeated measures over time, we will use multi-level regression analysis to examine the effect of the intervention on these outcomes, including in the models, a fixed effect for the intervention status (0 = pre-intervention, 1 = 6-month post-intervention, 2 = 12-month post-intervention) and calendar time of enrolment into the intervention for each participant, as well as a random effect of the Local Health District (LHD) to explore the degree of variation in the intervention effect by LHD. Our final model will exclude the random term in the presence of a statistically non-significant random effect. We will also consider participants are clustered within each LHD and use generalised estimating equations (GEE) approach in the regression analysis to account for the clustering.

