## Discussion

Asthma remains the most common chronic respiratory disease in children and adolescents in Australia and continues to have a high associated burden of care [1, 2]. Our model of care offers a solution to the current fragmented and inadequate Australian healthcare system. This model aims to standardise the care provided for children with asthma and provide easy access to in-depth educational resources and support tools for families, healthcare providers and community services so a child’s asthma can be managed effectively outside of a hospital setting and closer to home.

We have used a pre-post trial design, which will allow us to determine the changes in health services used due to our model of care. The pre-intervention period of health service utilisation for each participant will be incorporated as a temporal control. A notable strength of this design is that since the same group serves as its control, it can help control for individual differences that might confound the results in studies involving separate control groups. This can enhance the internal validity of the findings. Additionally, the gathered pre-intervention period data will incorporate five years to account for the disruption of the COVID-19 pandemic, which has been well documented to have resulted in an unseasonable decrease in asthma hospitalisations during lockdown periods [38].

In analysing our data, we will use an Interrupted Time Series Analysis (ITS) methodology. ITS analysis is one of the most effective quasi-experimental evaluation methods and has been used in many health intervention evaluations [39]. It makes full use of the longitudinal nature of the data, allowing us to control for time-varying confounders such as seasonality and co-occurring competing interventions, thereby addressing critical threats to internal validity and causal inference.

An added advantage of our methodology is integrating a theory-informed mixed-method process evaluation. This inclusion allows us to comprehensively grasp the obstacles and enablers of implementing this initiative within real-world practice, and facilitates the identification of strategies conducive to its sustained implementation [40]. Concurrently, we will undertake an economic evaluation to establish a viable rationale for healthcare organisations to allocate resources towards adopting the Asthma model of care. This will substantiate the tangible advantages of such an uptake on the Australian healthcare system.

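### The qualifying ED visit or admission is counted in the pre-period with no matching condition afterwards, so the ITS of ED visits and admissions is biased towards a fall at enrolment

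*Protocol article*

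**What the plan says.** **Entry rule.** For asthma, the Study population section sets this criterion: "presenting to ED on one or more occasions or admitted to the general paediatric ward on one or more occasion in the last 12 months". Box 1 repeats it.

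**Windows.** Aim 1, Data collection, compares "the period of up to 5 years prior to their enrolment into the program (pre-intervention") with "the period of up to 12 months following enrolment (post-intervention"). The comparator is internal, namely each site's own history: "time period of health service use for each participating site will serve as its own control for the post-intervention time period". Five years of history are used because of COVID-19 disruption.

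**Outcome and analysis.** Table 1 lists hospital admissions, ED attendances and GP visits as the primary outcome. The Data analysis section of Aim 1 states the method: "Interrupted time series (ITS) analysis will be used to assess the change in the time series patterns (intercept and slope) of health service use".

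**Claims for the design.** The Discussion argues that "since the same group serves as its control, it can help control for individual differences that might confound the results", and says that ITS deals with the main threats to internal validity. The limitations paragraph concedes that a one-group design limits comparison with usual care. It does not mention selection on the outcome.

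**The concern.** Two of the three primary components, ED attendances and admissions, also serve as the entry criterion. A child enters because the count was at least one in the last pre-year, and no such condition applies to the post-year. Even with an unchanged underlying rate, the selected group should fall back towards its usual level after enrolment.

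Being one's own control removes stable differences between children. It does not remove selection on a temporarily high count. ITS does not remove it either: the selected events sit just before the interruption, lift the end of the pre-series, and reappear as a drop in level at enrolment.

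At stake are the ED and admission results, the cost-effectiveness ratios in Aim 3 that set the same counts against the pre-implementation period, and the research question on State-wide scale-up that rests on both.

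**Working it through.** **1. The plan's own figures.** The sample size section gives 317 recruited, 15% attrition, 270 analysed and a before/after rate ratio of 2.6. The attrition step agrees to within one child: 270/0.85 = 317.6, and 317 × 0.85 = 269.45. The 270 itself cannot be reproduced, because no ED rate per child is stated; the 2.8% is a share of attendances. The usual rate L (visits per child-year) is therefore an assumption below, shown as a range. The argument does not depend on the 270.

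**2. The rules side by side.** The entry event lies in the 12 months before enrolment. The pre-window is up to 60 months ending at enrolment, so it contains the event. The post-window starts at enrolment and requires no event. The article describes no exclusion, washout or comparator selected by the same rule.

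**3. Five-year mean against 12 months after, no programme effect.**

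- *One event triggers enrolment.* Expected pre-rate = (5L + 1)/5 = L + 0.2; post-rate = L; ratio = (0.2 + L)/L.
- *Look-back only (at least one event in 12 months, common Poisson rate).* The last pre-year averages L/(1 − e^−L) and the other four average L; ratio = [4 + 1/(1 − e^−L)]/5.

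| L per year | Event-triggered | Apparent fall | Look-back only |
|---|---|---|---|
| 0.5 | 0.7/0.5 = 1.4 | 29% | 1.31 |
| 1 | 1.2/1 = 1.2 | 17% | 1.12 |
| 2 | 2.2/2 = 1.1 | 9% | 1.03 |

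**4. Segmented ITS, no programme effect.** Assumptions: 270 children selected for at least one event in the last 12 months, gamma frailty with shape 0.5, 60 pre-months and 12 post-months aligned on enrolment, Poisson model with level and slope terms and estimated dispersion.

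| Population mean, visits/year | Level ratio | p<0.05 |
|---|---|---|
| 0.2 | 0.45 | 99% of runs |
| 0.5 | 0.72 | 67% of runs |

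The ITS does not share the dilution in step 3, because the selected events cluster at the end of the pre-series.

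**5. Distance from index event to enrolment.** A second simulation added one index event per child, with underlying rates of about 0.19 to 1.0 per year. The median level ratio was 0.13 to 0.58.

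- Events spread over the 12 months before enrolment: significant in 99–100% of runs.
- Events spread over 3 months: significant in 34–89%.
- All events in the last pre-month: the estimate still fell by 48–87%, but the spike inflated the dispersion and no run was significant.

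**6. Remedies, in the setting of step 4.**

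- Dropping the index episode and the time from it to enrolment gives level ratios of 0.95–0.98, with 5% false positives.
- Dropping the whole 12-month look-back gives 0.97–1.00.
- With an assumed COVID dip (rate halved in months −40 to −19) and no COVID term, dropping the look-back gives a spurious *rise*: 1.99 at mean 0.2 and 1.94 at mean 0.5, significant in 69% and 91% of runs. Adding the term restores 1.00–1.01.

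**The case against.** **A large fall is not established.** A reader might set the artefact against the design ratio of 2.6. In a comparison of 12 months before with 12 months after, (1 + L)/L gives 3.0 at L=0.5, 2.0 at L=1, and exactly 2.6 at L=0.625. The article does not plan that comparison; it sets up to five years against 12 months, where the artefact is diluted as in step 3. Since L is not stated, no single size can be claimed. This objection stands.

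**A false positive is not certain.** The discharge pack and the text message within 7 days of discharge suggest enrolment close to the event, where step 5 shows that the test can lose significance. If the event were treated as time zero it would be in neither window, and an analysis plan not shown may say so. That limits the claim about p-values, but not the claim about the estimate: the windows as written include the event.

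**The whole primary result is not affected.** A reader might infer that every primary component would look favourable. GP visits are not an entry condition, and the programme encourages them. This stands.

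**ACT/C-ACT.** One might infer that the 4-week recall at baseline covers the exacerbation. Entry allows an event up to 12 months earlier and the interval to the questionnaire is not given, so overlap is possible but not shown.

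**The limitation is already conceded.** The article admits that a one-group design limits comparison with usual care, so it would be too strong to say that it ignores its lack of a control. The concession does not name this bias, and the same Discussion credits self-control and ITS with protecting validity.

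**Conclusion.** The concern holds for ED attendances and hospital admissions, and for the costs built on them. The stated entry rule and windows bias the comparison towards a fall, and nothing in the article corrects this.

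The size depends on unstated quantities. For the five-year mean it is a rate ratio of 1.4 to 1.1 for L from 0.5 to 2 if an event triggers enrolment, and less under a pure look-back rule. For the ITS it is a spurious level ratio of about 0.45 to 0.72, with p<0.05 in about 67 to 99% of runs, under the frailty, rates and enrolment-aligned time axis assumed in step 4. The documents do not support saying that the artefact equals the planned 2.6, that significance is assured, or that every primary component is affected.

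**What to change.** In the primary ITS of ED visits and admissions, and in the pre/post costs that use those counts:

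- Exclude the index episode and all time from it to enrolment from the pre-period, and adjust person-time to match.
- Include an explicit COVID-period term.
- Report two sensitivity analyses: removal of the whole 12-month look-back, only with the COVID term; and the full window as now written.
- State regression to the mean as a limitation, and qualify the Discussion's claim about self-control and ITS.
- Describe changes in ACT/C-ACT and quality of life from enrolment as uncontrolled change, because baseline may overlap the exacerbation.

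Cost: no new data, since the five-year history is already planned. The date of the index episode has to be identified for each child and the COVID period defined in advance. Some pre-period time is lost, and the headline reduction will be smaller.
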